### Patient retention and adherence

To develop professional relationships with participants, a specific research team member will be assigned to each participant for consistency across all visits. Participants will receive $30 for each on-site visit. Participants are allowed to miss up to two intervention visits during the intervention period. Missed visits will be recorded as non-adherent in the database and rescheduled immediately after the planned intervention period so that participants can complete all treatment sessions without substantial delay.

### Data analysis plan

Baseline demographic and clinical characteristics will be summarized for each treatment group. The primary analyses will be conducted on a modified intention-to-treat (ITT) sample, including all randomized participants who received at least one FES session. The efficacy of FES will be evaluated using ANCOVA to compare changes in HAM-D-17 scores from baseline to the final FES session between the active and sham groups, adjusting for baseline HAM-D-17 score and sex. Correlations between baseline and follow-up HAM-D-17 scores will be analyzed at the participant level. Similar analyses will be conducted for secondary clinical outcomes. Moreover, FES tolerability will be evaluated by summarizing overall dropout rates as counts and percentages. For dichotomous outcomes like remission, response, and AEs, between-group differences will be analyzed using odds ratios with 95% confidence intervals. Blinding effectiveness will be assessed by calculating Bang’s blinding index for rater and participants. Analyses stratified by sex and age will also be performed to explore potential subgroup differences.

Additionally, automated facial behavior analysis software (OpenFace) will be used to quantify Duchenne smile metrics derived from facial Action Units (AUs), including frequency, duration, and average activation intensity. Duchenne smiles will be identified based on the concurrent activation of AU12 (lip corner puller) and AU6 (cheek raiser). Descriptive statistics and group comparisons will be performed to examine differences in genuine smiling between the FES and sham groups. OpenFace is an open-source facial behavior analysis toolkit developed by researchers at the University of Cambridge and Carnegie Mellon University. Using computer vision and machine learning algorithms, it detects facial landmarks (e.g., eye, mouth, and eyebrow positions), estimates head pose, and quantifies facial muscle activity through the Facial Action Coding System (FACS) by identifying the presence and intensity of facial AUs. Participant videos will be processed using OpenFace to extract facial landmark coordinates and AU measurements. The output will consist of CSV files containing numerical facial behavioral data identified only by participants’ study IDs. These de-identified data will subsequently be used for statistical analysis.

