### Randomization and masking

Participants will be randomly assigned in a 1:1 ratio to receive either active FES or sham using a randomization schedule generated through a secure REDCap module. Block randomization, stratified by sex, will account for potential differences in response and tolerability. Personnel conducting outcome assessments and other blinded study procedures will not have access to the fixed block size or treatment assignments. Randomization will be conducted by the intervention staff, who will have access to group assignments as required to deliver and monitor the stimulation sessions. In an emergency, the study doctor may be informed of the participant’s group assignment if this information is necessary for clinical management.

Moreover, to preserve blinding, sensory and non-Duchenne-patterned sham stimulation will be utilized. Participants will be instructed to avoid interaction with one another throughout the study. Blinding effectiveness will be assessed after each session by asking participants and raters to indicate whether they believe the participant received active or sham FES.

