### Outcome measures and data collection

The primary outcomes include changes in depressive symptoms, measured by the HAM-D-17, a validated, semi-structured, clinician-administered interview for assessing the presence and severity of depression. The other primary outcome will assess tolerability and safety based on dropout, data completion, protocol adherence rates, and the frequency and nature of AEs and SAEs. Secondary outcomes include MDD response and remission rates, anxiety, quality of life, and sleep quality. These outcomes will be measured using the 16-Item Quick Inventory of Depressive Symptomatology – Short Form (QIDS-SR-16) [25], Generalized Anxiety Disorder-7 (GAD-7) [26], World Health Organization-5 Well-Being Index (WHO-5) [27], and Pittsburgh Sleep Quality Index (PSQI) [28]. Additional secondary outcomes include response (50% decrease in total HAM-D-17 score) and remission (HAM-D-17 < 7) rates and sustainability of these outcomes for up to 28 days post-stimulation. In addition, facial expressivity during video-recorded emotional recall interviews will be assessed as an exploratory outcome.

An independent assessor will administer the HAM-D-17 and complete the Concomitant Medication Record (CONMED) at baseline, at the end of each week during the randomized intervention period, and at each follow-up visit. Participants will also be queried daily about their experiences and any AEs or SAEs they may encounter. To monitor participant burden, an FES Experience assessment will be conducted at the end of each treatment week through REDCap. All secondary outcomes will be assessed at baseline, at the end of each week during the randomized intervention period, and during follow-up visits using REDCap. Emotional recall interview will be administered at baseline and at the end of each week during the intervention period.

This study will also collect necessary personal health information, including the participant’s name, date of birth, medical records (new or existing) related to psychiatric or medical conditions, current and past medications, surgical implants, and any illnesses or psychiatric procedures that could affect study participation. This information will be obtained from the participant, their physician, or their medical records.

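### Response, remission and AEs are given odds ratios with no stated covariates; adjusting remission for baseline HAM-D-17 and sex, and using risk differences for sparse AEs, would be a modest, cost-free gain

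*Protocol article*

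**What the plan says.** In the Data analysis plan, the ANCOVA of HAM-D-17 change is run "adjusting for baseline HAM-D-17 score and sex". The plan adds that "Similar analyses will be conducted for secondary clinical outcomes". Binary outcomes, with remission, response and AEs as the examples, then get a sentence of their own: "between-group differences will be analyzed using odds ratios with 95% confidence intervals". That sentence names no model, covariate or method for sparse cells.

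Outcome measures and data collection defines "response (50% decrease in total HAM-D-17 score) and remission (HAM-D-17 < 7) rates". Response is therefore relative to baseline, and remission is an absolute cut. Under Randomization and masking, sex is the stratification factor: "Block randomization, stratified by sex, will account for potential differences in response and tolerability". Success criteria counts the absence of a significant between-group difference in AE frequency or severity as a safety success. It places response and remission under the sustainability of effect.

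**The concern.** Response and remission come from the same scale as the primary outcome, yet the stated method carries neither of the covariates used for that outcome. Baseline severity should predict who ends below a fixed score of 7. It may also vary widely, because Eligibility criteria asks for a MADRS of at least 7 and sets no HAM-D-17 minimum. Sex was made a stratum because of expected differences in response and tolerability, but it is not named in the analysis of either.

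Two things are at stake. An unadjusted remission comparison leaves available information unused in a trial of 60, and its result can shift with a chance difference in baseline. For adverse events, the odds ratio is the only between-group method stated, and with few events it may give no usable interval.

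**Working it through.** The protocol gives no rate, odds ratio or power for response, remission or AEs, so it has no figure of its own to reproduce here. Whether 60 participants follow from the stated effect size and power is a separate matter; nothing below depends on it.

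**Inputs from the protocol.** 30 per arm, allocated 1:1; d = 0.5; two-sided 5%; the two outcome definitions; covariates baseline HAM-D-17 and sex. The expected 51 completers motivate a second case of 25 per arm.

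**Assumptions, not in the protocol.** Baseline mean 20, SD 5; sham endpoint mean 13, SD 6.5; baseline-endpoint correlation r = 0.3, 0.5 or 0.7; no sex effect. The treatment effect is 0.5 × 6.5 = 3.25 points.

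**Step 1: power.** There were 4,000 simulated trials per scenario. Logistic regression with treatment alone was compared with treatment, baseline and sex, using Wald tests. Rates came out at about 16% v 31% for remission and 28–31% v 52% for response.

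| Per arm | r | Remission, unadjusted → adjusted | Response, unadjusted → adjusted |
|---|---|---|---|
| 30 | 0.3 | 23.5% → 26.9% | 35.0% → 35.6% |
| 30 | 0.5 | 23.6% → 28.9% | 40.1% → 40.8% |
| 30 | 0.7 | 23.9% → 31.2% | 47.8% → 51.6% |
| 25 | 0.3 | 19.3% → 20.1% | 30.4% → 30.6% |
| 25 | 0.5 | 20.4% → 23.3% | 36.0% → 37.1% |
| 25 | 0.7 | 20.3% → 25.9% | 42.5% → 45.0% |

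At 30 per arm the gain is 3.4, 5.3 and 7.3 points for remission, and 0.6, 0.7 and 3.8 for response. With no treatment effect, rejection at 30 per arm was 2.4–2.6% unadjusted and 2.9–3.3% adjusted for remission, and 4.1–4.2% and 4.8–5.2% for response. Neither method inflates the error rate materially. Because no sex effect was assumed, the gain comes from baseline alone. A separate run with Firth-penalised Wald tests gave 28% to 33% for remission near d = 0.5, and no dependable gain for response (43% and 39%).

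**Step 2: chance imbalance.** The standard error of the baseline difference is 5 × √(2/30) = 1.29 points. With no treatment effect, expected remission in an arm is Φ((6.5 − m)/6.5), where m = 13 ± (1.29/2) × r × 6.5/5. Balanced arms give Φ(−1) = 15.9% each.

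- One SE, r = 0.3: 16.8% v 14.9%, odds ratio (0.149/0.851)/(0.168/0.832) = 0.87 against the arm that starts worse.
- One SE, r = 0.7: 18.2% v 13.8%, odds ratio (0.138/0.862)/(0.182/0.818) = 0.72.
- Two SE, r = 0.7: 20.6% v 11.9%.

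A difference of more than one SE arises in about one third of trials counting both directions, and so in about one sixth against the active arm. Response is already measured relative to baseline, so this step concerns remission.

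**Step 3: empty cells.** For true event rate p in both arms and 30 per arm, P(at least one arm empty) = 1 − (1 − (1 − p)^30)² and P(both empty) = (1 − p)^60.

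- p = 5%: 0.95^30 = 0.215, giving 38% and 4.6%.
- p = 2%: 0.98^30 = 0.545, giving 79% and 30%.
- p = 10%: 8% and 0.2%.

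The Wald interval uses √(1/a + 1/b + 1/c + 1/d), which fails when a cell is zero. Even without a zero, 3 v 1 events gives 3 × 29/(27 × 1) = 3.22, with interval 0.32 to 32.9.

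**The case against.** The strongest reply is that the plan never calls these odds ratios unadjusted. An adjusted logistic model also yields an odds ratio with a 95% interval, and the sentence on similar analyses for secondary outcomes could be taken to extend the adjustment. Covariates for secondary models and sparse-data methods are also often left to an analysis plan, which is not shown. This stands to the extent that a reader who concludes the sponsor has chosen a crude analysis goes beyond the text. It does not remove the point: binary outcomes have their own sentence, the method stated there carries no covariate, and the proposal is a better method rather than a request for more detail.

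Four other strong readings fail.

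- **Large power loss.** Gains of about 10 points for remission (52% to 62%, 71% to 81%) appear if effects of 4 or 5 points are assumed with baseline SD 5, slope 0.7 and residual SD 5. The endpoint SD is then √(0.7² × 25 + 25) = 6.1 and the change SD √(0.3² × 25 + 25) = 5.2, so d lies between 0.66 and 0.96, above the planned 0.5.
- **Bias.** Across randomisations the imbalance averages out, and the unadjusted type I error is kept.
- **Odds ratio undefined for rare events.** It is undefined only when both arms are empty. With one empty arm it is 0 or infinite, and exact or penalised intervals still exist.
- **High stakes for the success decision.** The protocol does not call response and remission key secondary outcomes. The between-group efficacy criterion rests on HAM-D-17 change, which is already adjusted, and Sample size concedes that power may be low for some secondary outcomes.

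**Conclusion.** The point holds in a limited form and is of low severity. As stated, the binary analyses carry neither baseline HAM-D-17 nor sex. If they are run that way, remission loses roughly 3 to 7 points of power at 30 per arm near d = 0.5 and is exposed to chance baseline imbalance; response loses little or nothing. At 25 per arm the remission gain is about 1 to 6 points. These sizes rest on the assumed baseline and endpoint distributions and on r between 0.3 and 0.7. Remission power stays low with either method.

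For AEs the issue is sparseness, not adjustment. The probabilities of empty arms are exact for the stated event rates, but the rates are assumptions. A common event, such as mild discomfort, might not be affected.

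**What to change.** Analyse remission, and response for consistency with the primary ANCOVA, by logistic regression with treatment, baseline HAM-D-17 and sex, using Firth penalisation if events are sparse. Keep the unadjusted odds ratio as a supporting figure and label the two clearly, since they estimate different quantities. For AEs and SAEs, report the risk difference with a score or exact 95% interval, without baseline adjustment: baseline HAM-D-17 has no evident role there, and extra covariates destabilise sparse models.

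The cost is a change of analysis wording. Both covariates are already collected, and no visit, measurement or sample size changes. Recruitment is under way and primary results are expected by June 2029, so the wording can be settled before any outcome data are analysed.

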### Participant withdrawal and study termination

Participants may withdraw their consent and discontinue the study at any time without penalty. Withdrawal may also be initiated by the participant’s physician or the investigator if continued participation is deemed to pose a significant risk. Discontinuation criteria include a worsening of depression (defined as a more than 25% increase in QIDS-SR-16 score compared to baseline across two consecutive assessments), developing active suicidal intent, attempting suicide, non-adherence to study procedures, or missing more than two FES sessions. Participants meeting exclusion criteria during the trial will also be withdrawn. All early withdrawals will be documented, and participants will be asked to provide feedback on their FES experience and undergo any recommended medical evaluations. If study termination or early withdrawal is due to an AE or SAE, the research team will assist the participant in obtaining appropriate medical care, and the PI will conduct follow-up as required.

The study will be paused if SAEs related to FES are identified. Premature termination may occur if significant risks to participants, protocol non-adherence, insufficient evaluable data, or device modifications are identified. In such cases, the research ethics board will be informed.

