### Eligibility criteria

Recruitment will take place through referrals to the Interventional Psychiatry Program (IPP) at St. Michael’s Hospital, Unity Health Toronto, as well as through approved advertisements and flyers. Sixty participants with unipolar, non-psychotic MDD, as determined by the Mini-International Neuropsychiatric Interview (MINI) [21], will be recruited. Eligible participants will be males and females aged 18–70 years. They must have a Montgomery–Åsberg Depression Rating Scale (MADRS) [22] score of ≥7 and no more than two failed treatment trials during the current major depressive episode. Eligible participants will be required to maintain a stable regimen of medication and psychotherapy for at least four weeks before the study, and have no plan to change them throughout the intervention period, and during the follow-up, as reported in the Antidepressant Treatment History Form (ATHF) [23].

Individuals will be excluded if they have received ECT, magnetic seizure therapy, or intravenous ketamine during the current depressive episode, or rTMS within the previous 28 days. Additional exclusion criteria encompass a diagnosis of fibromyalgia, a history of epilepsy or seizures, oral metallic orthopedic implants, or damaged or dysfunctional facial nerves. Psychiatric comorbidities warranting exclusion consist of past or present symptoms of mania, hypomania, mixed episodes, psychotic disorders, obsessive-compulsive disorder, post-traumatic stress disorder, active substance use or dependence (excluding nicotine and caffeine), neurodegenerative disorders, or dementia. Participants with current suicidal intent or plan (MADRS item 10 score ≥ 4) or inability to generate the Duchenne smile with FES will also be excluded. Additionally, individuals who do not speak English will be excluded from this RCT to ensure clear comprehension of study information, facilitate communication for addressing participant questions, and obtain informed consent effectively.

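### Withdrawal for worsening depression is not separated from leaving the study, so loss of the end-of-treatment HAM-D-17 score can depend on the outcome itself

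*Protocol article*

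**What the plan says.** All references are to the protocol article.

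- **Participant withdrawal and study termination.** The first criterion is tied to depression: "Discontinuation criteria include a worsening of depression (defined as a more than 25% increase in QIDS-SR-16 score compared to baseline", at two consecutive assessments. The list continues with "developing active suicidal intent, attempting suicide, non-adherence to study procedures, or missing more than two FES sessions". It adds: "Participants meeting exclusion criteria during the trial will also be withdrawn". For what follows withdrawal, the section says "participants will be asked to provide feedback on their FES experience and undergo any recommended medical evaluations", and it provides for follow-up by the principal investigator when an adverse event is the reason. It mentions neither continuation nor cessation of HAM-D-17 rating.
- **Data analysis plan.** The primary set is a modified ITT sample, "including all randomized participants who received at least one FES session". The analysis is an ANCOVA on HAM-D-17 change from baseline to the final FES session, adjusted for baseline score and sex.
- **Sample size.** The same ANCOVA is placed at day 20. Attrition of 15% is assumed, leaving about 51 completers.
- **Outcome measures and data collection.** HAM-D-17 is rated at baseline, at the end of each treatment week and at each follow-up visit.
- **Study design and setting.** The baseline visit and the four follow-up visits are remote.

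**The concern.** When a depression score triggers withdrawal, and withdrawal may end rating, the primary depression score goes missing for reasons related to its own value. An ANCOVA on one end-of-treatment change cannot use a participant who lacks that score, even if the participant belongs to the modified ITT set by definition. The set as defined (everyone treated at least once) and the set with usable data (about 51 of 60) then differ, and the difference is related to outcome.

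What is at stake is the purpose that the sample size section gives the trial, which is to detect a signal on HAM-D-17. Selective loss could hide a real signal or create a false one. Ratings that were never taken cannot be recovered by any later analysis plan, so the point has to be settled while recruitment is open.

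**Working it through.** **1. The plan's own figure.** 60 × (1 − 0.15) = 51 completers, as stated. Expected losses are 60 − 51 = 9.

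**2. Set-up for the size of the effect.** The article gives neither the share withdrawn for worsening nor the correlation between the trigger and the primary outcome, so both are assumed.

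- The HAM-D-17 change is standardised to SD 1 in each arm; a lower value is better.
- A second score, standing for the worsening trigger, correlates *r* = 0.5 to 0.9 with it and carries the same treatment effect in SD units.
- The worst fraction *w* of an arm on that second score is withdrawn and has no endpoint.
- The comparison is a difference in mean change without covariates. Baseline adjustment would alter the precision.

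With normal scores, the mean of those who remain is too favourable by *r* × k(*w*), where k(*w*) = φ(z) / (1 − *w*), z is the upper-*w* normal quantile and φ is the normal density. The bias in apparent benefit is *r* × [k(active) − k(sham)].

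**3. Common threshold, true effect 0.5 SD, 15% withdrawn overall.** One cut-off removes about 9.4% of active and 20.6% of sham participants.

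- k(active) = 0.184 and k(sham) = 0.360; the difference is −0.175 before rounding.
- *r* = 0.5: 0.5 − 0.5 × 0.175 = 0.41 SD.
- *r* = 0.9: 0.5 − 0.9 × 0.175 = 0.34 SD.
- With 5% withdrawn overall, the estimate is 0.42–0.46 SD.

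Simulation with 30 per arm and *r* = 0.7 gave power of about 30%, against 48% with no loss. Smaller numbers explain part of that fall: 25.5 per arm with the effect intact gives 42%. The rest is mainly dilution.

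**4. Unequal withdrawal, no true effect.**

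| Active / sham withdrawn | k(active) − k(sham) | Spurious benefit, *r* = 0.5 to 0.9 | Type I error, *r* = 0.7 |
|---|---|---|---|
| 20% / 10% | 0.350 − 0.195 = 0.155 | 0.08–0.14 SD | about 7% |
| 25% / 5% | 0.424 − 0.109 = 0.315 | 0.16–0.28 SD | about 13% |
| 15% / 15% | 0 | 0 | 5% |

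The sign reverses if sham loses more. The closed form agrees with the simulation to within 0.01 SD.

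**5. When the score would be lost.** If QIDS-SR-16 is counted weekly, two consecutive assessments can be met at week 2 at the earliest. A participant who first meets the rule at week 4 may already have the primary rating.

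**6. The time point.** The sample size section uses day 20; the analysis section uses the final FES session. For a participant who stops early, the second could be read as that person's own last session, so that an earlier weekly rating stands in for the endpoint. Missed sessions are also made up after the planned period, so the final session can fall after the planned end. The two statements define different endpoints for exactly the participants at issue.

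**The case against.** The strongest reply is that the article is silent rather than wrong. It never says that rating stops at withdrawal or that participants without an endpoint are deleted, and a condensed article may leave both to the full protocol. That stands in part: it is not established that withdrawn participants will have no further HAM-D-17. It does not remove the point, because what is stated is a depression-triggered rule under a withdrawal heading, with no separation of treatment from study participation, feeding a single-endpoint analysis.

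A reader might also infer several stronger claims that the documents do not support:

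- *All withdrawals are treatment failures.* Missed sessions, non-adherence and most exclusion criteria are not. Only worsening and suicidality are clearly related to outcome.
- *Withdrawal must differ by arm because of the smile criterion.* Eligibility excludes those for whom "inability to generate the Duchenne smile with FES will also be excluded", but nothing says that this is retested after randomization or judged only under active stimulation.
- *The bias is about 30% of the planned effect.* Suppose 10% of one arm would have changed by +3 points and the rest by −8. The arm's true mean is 0.9 × (−8) + 0.1 × 3 = −6.9 against an analysed −8.0, a gap of 1.1 points. That is a bias in one arm's mean and cannot be set against a between-arm effect of 0.5. The same loss in the other arm cancels it. With 5% lost there, that arm's gap is 0.55 and the net bias is 1.1 − 0.55 = 0.55 points.
- *The rule favours active FES.* A common threshold with a real effect does the opposite and dilutes it.

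Finally, baseline-adjusted ANCOVA is a sound primary analysis if the scores are collected, so a mixed model is not essential.

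**Conclusion.** The point holds in limited form. As written, the plan allows the primary score to be lost for reasons tied to depression, and the modified ITT label does not by itself prevent that. Neither the direction nor the size of the between-arm bias can be fixed from the article. Under the assumptions above, the result ranges from dilution of a true 0.5 SD effect to 0.34–0.41 SD (common threshold, 15% withdrawn), through no bias (equal loss, no effect), to a spurious benefit of 0.08–0.14 SD (20% active against 10% sham, no effect). These figures treat every modelled withdrawal as outcome-driven and lost before the endpoint. Missed-session withdrawals unrelated to mood, and triggers met only at week 4, would make them smaller. It is a cheap improvement worth making now, not proof that the trial's result will be biased.

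**What to change.** Leave the clinical stopping criteria as they are; they are not judged here. Change the following:

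1. State in the withdrawal section that stopping stimulation is not leaving the study. Unless consent is withdrawn, the scheduled HAM-D-17 and REDCap assessments continue remotely through week 4 and follow-up.
2. Include those scores in the primary analysis at one fixed week-4/day-20 time point, and reconcile the day-20 and final-session wordings accordingly.
3. For scores still missing, use the weekly HAM-D-17 already collected. One option is a mixed model for repeated measures over weeks 1–4 (baseline score, sex, arm by visit) with the week-4 contrast, as the primary or a supporting analysis.

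The cost is wording plus a few remote ratings. The number of people concerned is at most about 0.15 × 60 = 9, and fewer in practice because that figure is all-cause attrition and includes anyone who withdraws consent. HAM-D-17 is already rated at remote visits, so no new staff or procedure is needed.

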## Methods

### Study design and setting

This study is a single-site, double-blind, pilot RCT conducted at St. Michael’s Hospital, Unity Health Toronto. The study design follows the SPIRIT guidelines (Fig 1) [20]. Eligible participants will be randomly assigned to receive either 20 sessions of active FES or sham. Both groups will complete a total of 26 visits (Fig 2). Six visits, including a screening visit, a baseline visit, and four follow-up visits, will be conducted remotely via phone or video conferencing using the Zoom platform. The 20 intervention visits will take place on-site, with participants attending one stimulation session per day over 20 consecutive working days. A trained staff member will directly monitor stimulation sessions. AEs and depressive symptoms will be monitored daily. All baseline assessments, except the emotional recall interview, will be repeated at the end of each intervention week and at each follow-up visit. The emotional recall interview will be conducted at baseline and at the end of each intervention week only. The SPIRIT Checklist is available in S1 File. The study protocol (Version 1, dated 10 March 2026; approved by the St. Michael’s Hospital Research Ethics Board, REB No. 24–155) is available as S2 File.

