### Safety and adverse events monitoring

Participant safety during all FES sessions will be overseen by trained investigators, with a licensed physician available at every visit. All AEs will be systematically recorded, including their severity, causality, and outcomes. AEs will be assessed daily: 1) the severity of each AE will be graded as mild, moderate, or severe, 2) causality will be categorized as probable, possible, unlikely, not related, or unclassified. SAEs are defined as events leading to significant disability, death, congenital defects, hospitalization, or requiring intervention to prevent such outcomes. Any SAE will be reviewed immediately and reported in accordance with ethical guidelines.

The outcome of each AE will be recorded as recovered/resolved, recovering/resolving, not recovered/not resolved, recovered/resolved with sequelae, fatal, or unknown. The study physician will promptly evaluate any unexpected events requiring urgent attention. In the event of an AE, medical care will be facilitated for the participant, and follow-up will be conducted by the Principal Investigator (PI). The PI will review and initial the AE log within 72 hours of its completion. All AEs, regardless of their relationship to FES, will be documented, followed until adequate resolution, and graded for severity and causality.

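### The numeric rule for worsening depression can never be met by participants who start at or above 0.8 of the QIDS-SR-16 maximum

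*Protocol article*

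**What the plan says.** Under *Participant withdrawal and study termination*, the protocol article defines one numeric criterion for clinical deterioration: "worsening of depression (defined as a more than 25% increase in QIDS-SR-16 score compared to baseline across two consecutive assessments". The same section also names "developing active suicidal intent, attempting suicide, non-adherence to study procedures, or missing more than two FES sessions", and adds that "Participants meeting exclusion criteria during the trial will also be withdrawn". Separately, withdrawal may be initiated by the participant's "physician or the investigator if continued participation is deemed to pose a significant risk".

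Under *Eligibility criteria*, severity is bounded from below only: "They must have a Montgomery–Åsberg Depression Rating Scale (MADRS) [22] score of ≥7 and no more than two failed treatment trials". Suicidal intent or plan is excluded through a single MADRS item (item 10 at 4 or more), and psychotic disorders are excluded. Neither caps the total depression score, and QIDS-SR-16 has no entry limit.

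The QIDS-SR-16 is a secondary outcome, and *Outcome measures and data collection* sets the timing: "All secondary outcomes will be assessed at baseline, at the end of each week during the randomized intervention period", and again at follow-up. *Study design and setting* states that "AEs and depressive symptoms will be monitored daily", and *Safety and adverse events monitoring* describes oversight "with a licensed physician available at every visit".

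**The concern.** The criterion is relative to the participant's own baseline, but the instrument is bounded. The higher the baseline, the less room remains above it, and from some point a rise of more than a quarter no longer fits on the scale. Nothing in the eligibility criteria keeps such participants out.

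The sponsor chose to put a numeric rule beside the general discretionary clause, presumably so that sustained worsening would be noticed without depending on someone's judgement. For the most severely depressed eligible participants that second layer is absent, however much they deteriorate. The stake is the working of a stated safety rule, not the validity of the trial's comparison.

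**Working it through.** **No plan figure to reproduce.** The article gives no scale range, no baseline QIDS-SR-16 distribution and no operating characteristics for this rule.

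**Where the rule stops working.** Let M be the maximum of a zero-based scale and b the baseline. The rule needs a score above 1.25 × b, and a score is at most M. It is therefore reachable only if 1.25 × b < M, that is b < M / 1.25 = 0.8 M. At b = 0.8 M exactly, the maximum score is a rise of exactly 25%, which is not more than 25%, so the boundary itself is also unreachable. This holds for any M. Enumerating whole-number scores for several assumed maxima gives the first unreachable baseline:

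| Assumed M | First unreachable baseline |
|---|---|
| 21 | 17 |
| 24 | 20 |
| 27 | 22 |
| 30 | 24 |

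With M = 27, used from here on as an assumption, the lowest qualifying score is floor(1.25 × b) + 1:

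- b = 20: 1.25 × 20 = 25, so 26 is needed.
- b = 21: 1.25 × 21 = 26.25, so 27 is needed, twice running.
- b = 22: 1.25 × 22 = 27.5, so 28 is needed, which does not exist.

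**How many participants.** Unknown. As an illustration with every input assumed (normal baseline, mean 12 to 18, SD 4 to 5), the share at 22 or more is the normal tail above 21.5. It runs from 0.009 (mean 12, SD 4) to 0.242 (mean 18, SD 5), or about 0.5 to 14.5 of 60. The share at 26–27 runs from 0.0004 to 0.067, or about 0.02 to 4.0 of 60.

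**What a 2-point review prompt would do.** Assume four weekly scores, independent normal error with within-person SD 1.5 or 2, rounding to whole points, and a baseline equal to the true score. If each score meets the threshold with probability p, the chance of at least two consecutive qualifying scores among four is 3p² − 2p³. For a rise of at least 2 points and a true change d, p = 1 − Φ((1.5 − d) / SD). True scores are capped at 27, so a nominal +4 is at most +3 from 24 and +2 from 25.

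| Situation | p (SD 1.5 / 2) | Prompt fires (SD 1.5 / 2) |
|---|---|---|
| No true change, baseline 22–25 | 0.159 / 0.227 | 6.7% / 13.1% |
| True +4, baseline 22–23 | 0.952 / 0.894 | 99% / 97% |
| True +4 capped to +3, baseline 24 | 0.841 / 0.773 | 93% / 87% |
| True +4 capped to +2, baseline 25 | 0.631 / 0.599 | 69% / 65% |
| Current 25% rule, baseline 22 or more | 0 | 0% |

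These detection rates fall if the baseline itself is read with error. For comparison, a 1-point threshold would fire in 31–35% with no true change, which is why 2 points is the more sensible example.

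**What is and is not the ceiling.** At baselines 20 and 21 the current rule needs a 6-point rise in both cases and fires in about 7–13% for a true +4. Since 20 lies clear of the limit, the low rate at 21 reflects the ordinary relative threshold. Only the drop to exactly zero from 22 upward is due to the ceiling.

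**The case against.** The strongest reply is that these participants are already covered. The list of discontinuation criteria is introduced as non-exhaustive, the physician or investigator may withdraw anyone judged at significant risk, and suicidal intent, suicide attempt and newly met exclusion criteria are dealt with separately. Symptoms are monitored daily, an independent assessor gives the HAM-D-17 weekly, and a physician is available at every visit. The proposed remedy also ends in clinical judgement. All of this stands, and it is why the point is minor. It does not restore the missing layer, because none of these provisions states a numeric threshold for worsening depression as such. What the fix adds is a documented prompt.

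A second reply is that near-ceiling scores may be rare, given entry from MADRS 7 and at most two failed treatment trials. That also stands: the limits do not cap severity, but nothing in the article shows that high baselines will be common.

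A third is that the full protocol (S2 File, not shown) may handle deterioration in more detail. It may. But the article prints a specific definition, and that definition fails for part of the eligible population, so this is a stated rule with a flaw and not a detail left elsewhere.

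A reader might infer that the most severely ill participants are unprotected, or that the trial's efficacy result is compromised. The documents support neither: the safeguards above apply to everyone, and the criterion plays no part in allocation, masking or the primary ANCOVA.

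**Conclusion.** The point holds in a narrow form. The rule is void for every baseline at or above 0.8 of the scale maximum. That is algebra and needs no assumption beyond a bounded, zero-based scale. The translation to a baseline of 22 or more rests on an assumed range of 0–27. For non-suicidal, non-psychotic worsening in these participants, clinical judgement is the only remaining route to a withdrawal initiated by the trial.

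The size is uncertain. The 0.5 to 14.5 of 60 shown above rests wholly on assumed means and SDs and may overstate or understate the truth. It would also be wrong to read the 97–99% detection rate as applying up to baseline 25, since a true 4-point rise does not fit on the assumed scale from 24 upward. Severity: minor, a correction of safety wording.

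**What to change.** Keep the 25% rule and add one sentence to *Participant withdrawal and study termination*, along these lines: *Where 1.25 × baseline QIDS-SR-16 equals or exceeds the scale maximum, a sustained rise over baseline at two consecutive weekly assessments (for example at least 2 points, or scores at the maximum where a 2-point rise is not possible) prompts a documented study-physician review of whether to continue; withdrawal is not automatic.* No review is needed when the score has improved. The 2-point figure is a suggestion for the sponsor to set. If the full protocol already contains such a rule, it should be carried into this definition.

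The cost is one sentence by amendment while recruitment is ongoing. It uses the weekly QIDS-SR-16 and the study physician the trial already has, and the earliest prompt is at the end of week 2. The downsides are modest:

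- Noise alone prompts a review in about 7–13% of such participants at baselines up to 25, if within-person SD is 1.5 to 2 (assumed).
- At 26 and 27 the fallback of scores at the maximum is less specific. With no true change, p is 0.369 / 0.401 at 26 and 0.631 / 0.599 at 27, so 3p² − 2p³ gives about 31–35% and 65–69%. Few participants, perhaps none, would start there.
- A step remains between a baseline of 21, which needs a 6-point rise for discontinuation, and 22, where 2 points prompts a review. The consequences differ (discontinuation against review), but the sponsor may wish to smooth the step when setting the threshold.
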